Aim 1 (to compare/contrast the nature of patient-provider communication by patient race) examines Path A in our conceptual model. To test Path A, first, we will examine a numerical and graphical summary of descriptive statistics that will inform the distribution of the 15 outcomes (14 categorical variables and the overall patient-provider communication) and that may require data transformation. Then, we will conduct two separate analyses for communication and linguistic patterns. To examine how genetic counseling providers’ communication style differs by patient race, we will identify covariates by conducting bivariate correlations among all 15 outcomes and factors that were assessed in the baseline surveys (e.g., provider/patient demographics including sex, provider professional characteristics, patient perceived discrimination). Next, we will estimate a linear regression model for each outcome with the main effect of patient race, the main effect of care modality, a two-way interaction between patient race and care modality, and covariates identified as highly correlated with the outcomes. We will use GEE (which controls for the dependence in outcomes due to patients nested within providers) in these regressions, instead of multilevel modeling (which models the nonindependence in data), because there will not be enough upper-level units (i.e., counselors) to model random effects in our data. We will use the Bonferroni correction [93, 94] to address family-wise errors due to multiple comparisons. To examine which specific linguistic patterns differ by patient, we will conduct analyses in similar steps described above. First, we will identify highly correlated covariates by computing bivariate correlations among all quantified linguistic patterns and factors assessed in the baseline surveys. Next, we will conduct a regression for each quantified linguistic pattern with the main effect of patient race, the main effect of care modality, a two-way interaction between the two, and covariates using GEE and the Bonferroni correction. Type of regressions will depend on the measurement units.

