Aim 2 (to compare/contrast the clinical discussion content by patient race) examines Path B in our conceptual model. We will examine which topics significantly differ between Black and White patients. First, we will identify covariates that may impact clinical discussion content by computing bivariate correlations among all topics and factors assessed in the baseline surveys. All significant factors will be included in the main analyses as covariates. In the main analyses, we will conduct a logistic regression (the dichotomous outcome) and a linear regression (the continuous outcome) for each topic with the main effect of patient race, the main effect of care modality, a two-way interaction between the two and covariates using GEE and the Bonferroni correction.

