Aim 3 (to quantify the role of each type of counselor bias in patient-provider communication and clinical discussion content) examines Paths C and D in our conceptual model. Analyses will be carried out in three steps. In Step 1, we identify covariates associated with patient-provider communication or clinical discussion content. We will compute correlations among all facets of patient-provider communication/clinical discussion topics identified in Aims 1 & 2 and factors assessed in the baseline surveys (e.g., provider/patient demographics, provider professional characteristics, patient perceived discrimination). In Step 2, we compute partial correlations between all forms of provider bias and aspects of patient-provider communication/clinical discussion topics identified in Aims 1 & 2, controlling for covariates that were significantly associated with any of the provider behaviors. In Step 3, we conduct two regressions for each of the specific aspects of patient-provider communication and clinical discussion topics that remain statistically significant in Step 2. One regression will focus on the role of provider prejudice and will consist of four main effects (patient race, provider implicit prejudice, provider explicit prejudice, care modality), all six combinations of two-way interactions, all four combinations of three-way interactions, and one four-way interaction among all predictors. The second regression model will focus on the role of provider stereotyping and will consist of four main effects (patient race, provider implicit stereotyping, provider explicit stereotyping, care modality), all six combinations of two-way interactions, four combinations of three-way interactions, and one four-way interaction among all predictors. The type of each outcome, summarized in Table 4, will determine the regression model to analyze. The regressions will also include the same set of covariates as in Step 2. All four types of provider bias will be grand-mean-centered. We will use GEE and the Bonferroni corrections in analyses. The provider communication styles that remain statistically significant in Step 3 are considered as key communication styles that contribute to racial disparities in the cancer genetic counseling process and reflect provider bias.

**Table 4 Tab4:** An overview of the outcomes and analyses for each aspect of patient-provider communication and clinical discussion content

Outcome types	Variables	Analytical approaches

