Continuous: Likert scale	*Patient-provider communication* (Provider communication style; The overall quality of patient-provider communication)	Linear regression with GEE
Continuous: Frequency	*Patient-provider communication* (Each type of silence; Each type of adjacency pairs; Each type of problems)	Poisson regression with GEE
Continuous: Proportion	*Patient-provider communication* (Topics initiated by providers; Primary units allocated to providers; Silence followed by provider talks; Repairs initiated by providers; Problems repaired by providers)	Linear regression with GEE
Continuous: Duration	*Patient-provider commu*nication (Each type of silence) *Clinical discussion con*tent (The amount of time spent on discussing a given topic)	Linear regression with GEE
Dichotomy	*Clinical discussion content* (The presence/absence of a given discussion topic)	Logistic regression with GEE
Multiple categories	*Patient-provider communication* (The primary units of turns)	Multinomial logistic regression with GEE

Finally, Aim 4 (to quantify the impact of patient-provider communication/clinical discussion content with patient-centered outcomes) examines Paths E and F in our conceptual model. The analyses will be carried out in steps similar to those in Aim 3. In Step 1, we will identify covariates associated with patient-centered outcomes by computing correlations among all aspects of patient-provider communication/clinical discussion topics and factors assessed in the patient baseline survey, the provider baseline survey, and the provider post-encounter survey. In Step 2, we will compute partial correlations between all aspects of patient-provider communication/clinical discussion topics identified in Aims 1 and 2 and patient-centered outcomes while controlling for covariates identified in Step 1. In Step 3, we will conduct a linear regression with GEE and Bonferroni correction for each self-reported outcome (e.g., trust, satisfaction, therapeutic alliance) and a logistic regression with GEE for behavioral outcome (genetic testing completion). All regressions will include the same set of predictors (aspects of patient-provider communication/clinical discussion topics that remain significant in Step 2, and care modality) and covariates. Aspects of patient-provider communication/clinical discussion topics that remain significant in Step 3 are considered as potentially important intervention points for reducing racial disparities in patient-centered outcomes.

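### Optional efficiency gain: Holm's step-down procedure gives the same family-wise control as the planned Bonferroni correction and can carry more true differences into Aims 3 and 4

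*Protocol article*

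**What the plan says.** All of this is in the protocol article, Statistical analysis.

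- **Aim 1, ratings.** The outcomes are "the 15 outcomes (14 categorical variables and the overall patient-provider communication"), one regression each. The article then says "We will use the Bonferroni correction" and gives the purpose as control of family-wise error across multiple comparisons.
- **Aim 1, linguistic patterns.** "we will conduct a regression for each quantified linguistic pattern with the main effect of patient race", again with Bonferroni. Table 3 lists 4 + 2 + 2 = 8 patterns.
- **Aim 2.** Each topic gets a logistic and a linear model, with "a two-way interaction between the two and covariates using GEE and the Bonferroni correction". The number of topics is not given.
- **Aim 3.** "We will use GEE and the Bonferroni corrections in analyses". The number of tests depends on what survives Step 2.
- **Aim 4.** "a linear regression with GEE and Bonferroni correction for each self-reported outcome". The logistic model for genetic testing completion carries no such wording.

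No step-down version is named, so single-step Bonferroni is the natural reading. The article gives no alpha level and no correlations among the outcomes, and it promises no simultaneous confidence intervals.

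**The concern.** The stated goal is family-wise error control. Two procedures reach it with the same guarantee and under the same conditions (none on dependence), and the plan names the one that can never reject more.

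This would usually be a footnote. It deserves a line here because Aims 1 and 2 act as a filter. Step 2 of both Aim 3 and Aim 4 takes up the aspects of communication and the topics identified in Aims 1 and 2. If identified means significant after correction, which is the natural reading, a real racial difference missed in Aim 1 or 2 is never related to provider bias or to patient-centered outcomes. The number of true differences that pass therefore matters, not only whether any does. Holm's advantage lies in the second and later rejections.

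**Working it through.** **No figure in the plan to reproduce.** The article gives no power for the race comparisons or for the correction. Its one power statement (0.80 at d = 0.2) concerns provider implicit prejudice and does not mention multiplicity, so nothing below rests on it.

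**Inputs**
- From the article: m = 15 ratings; m = 8 linguistic patterns (counted from Table 3); 220 patients in approximately equal racial groups, taken as 110 per group.
- Assumed: family-wise alpha 0.05 two-sided; equal correlation 0.6 among the 15 test statistics; no clustering penalty; d from 0.2 to 0.5; 5, 10 or all 15 ratings truly different.

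**Rules compared**
- Bonferroni: reject each hypothesis with p ≤ 0.05/m. For the ratings this is 0.05/15 = 0.0033; for the linguistic patterns 0.05/8 = 0.00625.
- Holm: order the p-values from smallest to largest and compare the i-th with 0.05/(m − i + 1), stopping at the first failure. For the ratings the thresholds are 0.05/15, then 0.05/14 = 0.0036, and so on up to 0.05.

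Holm's first threshold is Bonferroni's and later ones are looser, so Holm rejects everything Bonferroni does. If Bonferroni rejects nothing, neither does Holm, so the chance of at least one rejection is identical.

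**Bonferroni power by formula.** The standard error of a standardized difference is √(2/110) = 0.135. At d = 0.4 the z statistic is centred at 0.4/0.135 = 2.97. The two-sided critical value at 0.0033 is 2.94. Power is P(Z > 2.94 − 2.97) ≈ 0.51.

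**Holm power by simulation** (equicorrelated z statistics, average power per true effect, 15 ratings):

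| d | Bonferroni | Holm, 5 true | Holm, 10 true | Holm, 15 true |
|---|---|---|---|---|
| 0.2 | 0.07 | 0.08 | 0.08 | 0.09 |
| 0.4 | 0.51 | 0.53 | 0.56 | 0.63 |
| 0.5 | 0.78 | 0.80 | 0.83 | 0.88 |

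At d = 0.3 the change is from 0.24 to 0.25 with 5 true effects and to 0.27 with 10.

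**In aspects carried forward at d = 0.4.** With 10 true differences, 10 × 0.51 = 5.1 pass under Bonferroni and 10 × 0.56 = 5.6 under Holm. With 15 true, the figures are about 7.7 and 9.4.

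**Eight linguistic patterns at d = 0.4, same assumptions.** Power goes from 0.59 to 0.64 with 5 true and to 0.70 with all 8 true. This is only illustrative, since Table 3 assigns Poisson models to two of the eight.

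**Error control.** With 10 of 15 ratings truly different, the family-wise error among the other five is about 0.014 under Bonferroni and about 0.03 under Holm. Holm uses more of the allowance and stays below 0.05. With no true differences the two are identical: about 0.03 at correlation 0.6 and 0.020 at 0.8.

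**At least one rejection.** At d = 0.4 with 5 true effects the chance is 0.82 under both.

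**The case against.** **Bonferroni is not wrong.** It is pre-specified, valid under any dependence, and does what the article asks of it. Nothing in the article is contradicted, and no conclusion becomes invalid if this point is ignored. That stands in full, and it limits the point to an optional refinement.

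**The gain may be small.** With 5 of 15 ratings truly different it is 1 to 2 points at d = 0.3 to 0.5. At d = 0.2, the only effect size the article states (and for another effect), it is under 2 points even if all 15 differ. Gains of 10 points or more need all 15 to differ at d = 0.4 to 0.5. Ignoring patients nested within providers also flatters the absolute power figures. All of this stands. A many-true pattern is not far-fetched, since Path A predicts poorer communication for Black patients generally and the same coders give all the ratings, but the documents cannot show how many ratings will differ.

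**A tempting stronger argument fails.** A reader might infer that the ratings are correlated, that Bonferroni is therefore conservative, and that Holm recovers the loss. Holm does not use the correlation: its global-null error equals Bonferroni's at every correlation. The documents also give no correlations, and the rating list mixes categories of opposite valence, such as irritability and warmth. Correlation is no reason to prefer Holm.

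**Intervals.** Bonferroni has simple matching simultaneous intervals; Holm does not. Bonferroni intervals shown beside Holm decisions can include the null for a rejected hypothesis. This is a real but small cost, because the article promises only significance decisions.

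**Conclusion.** The point holds as an optional, nearly free efficiency improvement. Holm gives the guarantee the plan wants and cannot reject fewer hypotheses. Because Aims 1 and 2 feed Aims 3 and 4, the added rejections can keep some real differences in the later analyses.

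The benefit for the 15 ratings ranges from almost nothing (few true effects, or d = 0.2) to about 11 or 12 points of average power per true effect (all 15 different at d = 0.4). It is nil for the first rejection. These figures rest on the assumed alpha, correlation, group sizes and absence of clustering.

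A reader might infer that the plan's multiplicity control is defective. The documents do not support that: family-wise error is controlled as stated. Nor does the point extend to the Aim 4 model for genetic testing completion, to which the article attaches no Bonferroni correction.

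**What to change.** In Statistical analysis, replace the Bonferroni correction with the Holm step-down procedure wherever it is named: both Aim 1 analyses, Aim 2, Aim 3 and the self-reported outcomes of Aim 4. Keep the families as they are.

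The change needs no new data and loses no error control. If simultaneous intervals are wanted, Bonferroni intervals can still be reported, with a note that they may not match the Holm decision for every outcome. Leaving Bonferroni in place would also be defensible.

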Our conceptual model of racial disparities in the cancer genetic counseling process is applicable to many genetic counseling encounters. However, this research will focus on pre-test cancer genetic counseling encounters for both theoretical and methodological reasons. Traditional cancer genetic counseling involves at least two encounters with patients having genetic testing: [1] a pre-test session involving risk assessment and informed consent; and [2] a post-test session in which risks and medical management are re-assessed in light of genetic test results. More cancer genetic testing is being facilitated by non-genetics providers (e.g., direct-to-consumer testing, mainstream testing by oncology providers). In such cases, genetic counselors may shift to involvement only after testing is completed, and often only if patients test positive. However, we chose to focus on pre-test genetic counseling sessions for a number of reasons. First, the counseling elements in pre-test sessions are more uniform than in post-test sessions, especially in light of multigene panel testing consent, which, by necessity involves discussions that are often not specifically focused on individual genes and related medical management implications [43]. Focusing on pre-test cancer genetic counseling encounters also minimizes inherent variability across pre- vs. post-genetic testing contexts as well as across different areas/specialties of genetic counseling, providing greater ability to test our conceptual model. Second, for about nine out of 10 referred patients, genetic test results will be negative; [2] in most of these cases, the risk assessment and medical management recommendations content will remain largely unchanged. Finally, studies show that genetic testing completion is lower when pre-test counseling is provided by genetics providers, [44] compared with non-genetics providers. By focusing on pre-test genetic counseling, we can gain insight into predictors of genetic testing completion, especially whether racial bias plays a role. After validating our conceptual model in the context of pre-test cancer genetic counseling, our future work can examine whether this model is generalizable to other genetic counseling contexts. Such empirical evaluation of the generalizability of the conceptual model will further contribute to theory development.

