#### Topic comprehensiveness of clinical discussion

Next, we will assess the extent to which topics discussed during clinical encounters are consistent with key topics included in the National Cancer Institute’s (NCI) Cancer Genetics Risk Assessment and Counseling (PDQ®)-Health Professional Version [70]. To do this, two genetic counselors on our team will create a topic codebook based on the PDQ®-Health Professional Version. The codebook will provide coding procedures and rules as well as descriptions and examples of each topic. While the codebook is being developed, two coders will unitize the verbatim transcripts into discrete topics or focal ideas/themes. The coders will be first trained on the unitization with a few transcripts before they start unitizing all transcripts. They will meet every 5 transcripts to discuss and solve discrepancies in the identified thought units. After all the verbatim transcripts are unitized into discrete topics, two coders will be trained on the codebook until they achieve consensus and then code all transcripts independently, while meeting every 10 transcripts to discuss discrepancies and reach consensus. We will use consensus estimates for two reasons. Methodologically, discussion topics are discrete categories [71]. Clinically, providers are expected to discuss with patients each topic clearly and with no ambiguity. Finally, for each encounter, we will create dichotomous (a given topic discussed/not discussed) and continuous (the total amount of time spent on discussing a given topic in seconds) outcomes.

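### Aim 2 fits the race-by-modality logistic GEE to every discussed/not-discussed topic, with no provision for topics so common or so rare that a cell has no variation

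*Protocol article*

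**What the plan says.** The section on topic comprehensiveness defines two outcomes per encounter and topic: "we will create dichotomous (a given topic discussed/not discussed) and continuous (the total amount of time spent on discussing a given topic in seconds"). It does so for the topics from the NCI reference and again for additional topics found during coding.

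Under Statistical analysis, Aim 2, the plan is that "we will conduct a logistic regression (the dichotomous outcome) and a linear regression (the continuous outcome) for each topic with the main effect of patient" (that is, race). Modality enters as a second main effect, and the same sentence then adds "a two-way interaction between the two and covariates using GEE and the Bonferroni correction". On covariates: "All significant factors will be included in the main analyses as covariates". Table 4 repeats logistic regression with GEE for presence or absence of a topic. Aim 3 Step 3 puts topics that survive screening into models with up to a four-way interaction.

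The article states no minimum frequency and no exact or penalised alternative. The one planned look at distributions, under Aim 1, concerns the 15 communication outcomes and not the topics. Neither the GEE working correlation nor the variance estimator is named.

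**The concern.** With race, modality and their product in a logistic model, each of the four race-by-modality cells needs both outcomes present. If every encounter in one cell contains the topic, or none does, the coefficient has no finite estimate. The software then either reports failure or stops at a very large coefficient. In the second case the usual GEE sandwich standard error does not grow with the coefficient, so the Wald p-value is tiny although nothing differs by race.

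Aim 2 is meant to find which topics differ between Black and White patients, and its list is the entry to Aims 3 and 4. A topic could be listed because a cell is empty. A topic whose fit fails has no defined status.

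**Working it through.** **Plan's own figure.** None exists for this analysis. The stated power of 0.80 concerns provider prejudice and communication style.

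**Inputs from the article.** 220 patients; at least 15 providers; about equal numbers of Black and White patients per provider, so about 110 each.

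**Assumptions, because the article gives no figure.** Topic coverage p from 80% to 99%, and 5% for a rare topic; modality split 50/50 (four cells of 55) or 20/80 (cells of 22, 22, 88, 88); 20 topics, giving 0.05/20 = 0.0025; no covariates.

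**Step 1: chance that at least one cell is all-discussed.** Even split: 1 − (1 − p^55)^4. At p = 0.95, p^55 = 0.0595 and 1 − 0.9405^4 = 0.218. For 20/80: 1 − (1 − p^22)²(1 − p^88)².

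| Coverage | 50/50 | 20/80 |
|---|---|---|
| 80% | 0.0% | 1.5% |
| 90% | 1.2% | 18.7% |
| 95% | 21.8% | 55.2% |
| 97% | 56.4% | 79.3% |
| 98% | 79.8% | 91.1% |
| 99% | 96.7% | 98.6% |

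By symmetry these figures also hold for topics at 20%, 10%, 5%, 3%, 2% and 1%.

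**Step 2: why the standard error collapses.** Take independence correlation and a cell of n encounters, all discussed, n_c of them with provider c. Each residual is 1 − μ. The sandwich variance of the cell's log-odds is (1 − μ)² Σn_c² / [nμ(1 − μ)]² = Σn_c² / (nμ)². As μ approaches 1 this tends to Σn_c²/n², not to infinity. Spread evenly over 15 providers it is 1/15 = 0.067, a standard error of 0.26, while the log-odds itself diverges.

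**Step 3: null simulation.** No race or modality effect, 15 providers, no provider clustering, robust standard errors, 200 data sets per row. Entries are counts out of 200; false results are p < 0.0025 among converged fits. The nominal expectation per term is 0.0025 × 200 = 0.5.

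| Coverage, split | Empty cell | Failed, indep. | Failed, exch. | False race, indep. | False race, exch. | False interaction, indep. | False interaction, exch. |
|---|---|---|---|---|---|---|---|
| 90%, 50/50 | 3 | 1 | 2 | 0 | 1 | 2 | 1 |
| 95%, 50/50 | 42 | 21 | 22 | 1 | 13 | 11 | 19 |
| 98%, 50/50 | 161 | 57 | 71 | 20 | 79 | 21 | 87 |
| 5%, 50/50 | 47 | 15 | 29 | 2 | 11 | 9 | 17 |
| 90%, 20/80 | 44 | 17 | 19 | 1 | 22 | 18 | 25 |
| 95%, 20/80 | 121 | 26 | 64 | 1 | 44 | 49 | 57 |
| 98%, 20/80 | 177 | 51 | 98 | 14 | 69 | 40 | 77 |

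- A separate run of 300 data sets (exchangeable, even split) gave false race results in 29/300 = 9.7% at 95% and 99/300 = 33% at 98%. All came from data sets with an empty cell; without one, the counts were 0/236 and 0/63.
- A third run over 95 to 98% coverage gave 0.5 to 13% (independence) and 12 to 31% (exchangeable) for race, with 8 to 45% of fits failing.
- With a provider intraclass correlation of 0.1 and an even split, the exchangeable counts for race were 34/200 = 17% at 95% and 82/200 = 41% at 98%.
- A bias-reduced sandwich did not help. Model-based standard errors gave no false results, which points to the sandwich variance as the source.

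**The case against.** **Coverage near 100% is not stated.** A reader might infer from "Clinically, providers are expected to discuss with patients each topic clearly and with no ambiguity" and from "the counseling elements in pre-test sessions are more uniform than in post-test sessions" that most topics will be near-universal. The documents do not support that. The first sentence is a reason for consensus coding and a norm for practice, not a forecast. The second is only a comparison with post-test sessions. The conceptual model itself expects poorer discussion content for Black patients. So the finding is conditional on a topic's rate.

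**Size depends on open choices.** At 95% coverage with independence correlation and an even split, the race term was falsely significant in only 1 of 200 data sets; most false results there were interactions. This stands, and is why a range is given.

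**The artefacts are visible.** At 97 to 99% coverage the false results had log-odds coefficients of about 20 or more, and a failed fit announces itself. True, but the article does not say what the analyst then does.

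**Reach.** A reader might infer that Aim 2 is lost for such topics, or that false disparities pass straight through to Aims 3 and 4 and to training content. Neither follows. The seconds outcome keeps a range for near-universal topics, although for rare ones it is mostly zeros. Aims 3 and 4 screen topics again by partial correlation, where an empty cell gives no advantage.

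**Ordinary SAP detail.** A condensed article may leave sparse-data handling to a SAP, which is not shown here. But this one fixes a model for every topic, and applying it as written gives wrong answers for some. That goes beyond missing detail.

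**Conclusion.** The concern holds in conditional form. For any topic at about 95% coverage or more, or 5% or less, the stated model often cannot be fitted or returns false significance that Bonferroni does not remove. The threshold moves to about 90% or 10% if one modality has only about a fifth of encounters. Under the null at 95 to 98% coverage, the race term was falsely significant at 0.0025 in about 0.5 to 13% of data sets with independence correlation and 12 to 31% with exchangeable; other exchangeable runs spanned 6.5 to 41%. With an even split the problem is small at 90% and negligible at 80%.

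These figures rest on assumed topic rates, 20 topics, the two modality splits, and no covariates; adding covariates would make the data sparser. How many topics are affected cannot be told from the documents.

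**What to change.** State before topics are coded that, when any race-by-modality cell has no variation or very few events or non-events (for example, fewer than 5), the race-by-modality logistic GEE is not used for that topic. Instead:

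- Test the race main effect with a method valid for sparse data that respects clustering: an exact or permutation test of race stratified by provider, or a Firth-penalised main-effects model that accounts for provider. The stratified exact test stayed at or below 0.5% false positives at 0.0025 in every null setting run.
- Keep the topic in the Bonferroni family, report counts by race and modality, and keep the seconds analysis.
- Apply the same rule to dichotomous topics in Aim 3 Step 3.

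A pooled band such as 10 to 90% coverage, with topics outside it dropped from the family, would be a poor substitute. If 110/110 White and 97/110 Black encounters contain a topic, pooled coverage is 207/220 = 94%. Fisher's p is 2·C(110,13)/C(220,13) = 0.00017, yet the difference would go untested or be tested without correction.

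Cost: a paragraph of wording, and no race-by-modality estimate for those topics, which the data cannot supply. A stratified exact test also drops the other covariates. The example threshold of 5 is strict: at 90% coverage each cell of 55 expects 55 × 0.10 = 5.5 non-events, and only 30 of 200 simulated data sets (even split, no clustering) kept the full model. At 95% and 98% none did.
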